## Methods and analysis

### Overview of study design

The prospective cohort study described in this protocol is one of several formative research activities conducted as part of the PEARLS platform. The additional research activities (protocols reported elsewhere) include mixed-methods research with health workers, women and health systems stakeholders to identify challenges and the feasibility of implementing pre-eclampsia risk screening and AI-ultrasound,^5^ and two prospective cohorts (one is Ghana, Kenya and South Africa^4^ and a second in India) to evaluate the prognostic accuracy of a restricted variable-FMF risk screening tool.

This study uses a prospective cohort to evaluate accuracy of the IU ScanNav FetalCheck model at different gestational time points. The study will be implemented at selected study facilities in Ghana, Kenya and South Africa. Participating facilities are those with a trained, expert sonographer who will perform conventional ultrasound scans and fetal measurements (CRL, biparietal diameter (BPD), head circumference (HC), abdominal circumference (AC), femur length (FL) as required), in accordance with International Society of Ultrasound in Obstetrics and Gynaecology (ISUOG) standards.^19
20^ The study recruitment will begin in April 2025 and is expected to be completed in Q2-3 2026.

### Patient and public involvement

Two members of the PEARLS platform steering committee represent patient advocacy organisations and contributed to the development of this protocol. They will continue to provide oversight throughout study implementation and will contribute to interpretation and dissemination of findings. Patients and the public were not directly involved in selecting outcomes or designing data collection tools, and they will not be involved in conducting the study.

### Study setting

The study will be conducted in Ghana, Kenya and South Africa. In Ghana, University of Ghana Medical School investigators will collect data from one tertiary referral hospital, two district hospitals and one primary health facility in the Greater Accra Region. In Kenya, University of Nairobi investigators will collect data from two tertiary/county referral hospitals and three secondary hospitals in Kiambu County, Kakamega County and Kisumu City. In South Africa, University of Cape Town investigators will collect data from four midwife obstetrical units in Cape Town’s Metro West area. The full list of facilities can be found in online supplemental appendix A.

#### Training and standardisation

All study sonographers will be accredited to ensure gold-standard measurements are standardised across study sites. At each participating facility, a local sonographer trained in conducting fetal ultrasound scans according to both national and ISUOG standards^19
20^ will be identified. Prior to the study commencing, the study sonographers will receive training on the PEARLS protocol and procedures from ultrasound advisors (expert clinician-trainers who are maternal-fetal medicine consultants), as well as being provided with a detailed ultrasound training manual outlining exactly how each image should be acquired. Study sonographers will be accredited by these experts using standard ISUOG quality assessment and criteria. All study scans (experimental and control) are performed using the GE VScan Air ultrasound system (two-dimensional grayscale ultrasound with a curvilinear transabdominal probe).^21^ Following the training, each sonographer will submit 10 CRL images from scans conducted in the first trimester (<14 weeks) and 10 s trimester scans (containing the four biometric measurements: BPD, HC, AC and FL) from scans conducted in the second trimester (14–28 weeks). Each image will be reviewed by the ultrasound advisors and scored according to the INTERGROWTH 21st scoring criteria^22
23^ (table 1). Individual scans will be deemed suitable for the study if for HC, BPD, AC and CRL the image has met at least four out of the six quality assessment criteria. For FL, a scan must meet at least two out of the four quality assessment criteria to be deemed suitable for study purposes. A study sonographer will be accredited only if over 80% of their submitted scan images meet the quality assessment standards. Where discrepancies in scoring arise, a third ultrasound advisor will review scans and differences in scoring resolved via discussion.

**Table 1 T1:** Quality assessment criteria for scans obtained by study sonographers for accreditation by study ultrasound advisors. Quality assessment criteria are informed by INTERGROWTH-21st^22
23^

	Fetal biometric measurement			
Quality assessment	CRL	BPD/HC	AC	FL
Criteria 1	Mid-sagittal section	Symmetrical plane	Image shows the stomach bubble	Both ends of the bone clearly visible
Criteria 2	Fetus is in the horizontal orientation	Plane showing thalami	Image shows umbilical vein along 1/3 of the abdomen	>45 angle to the horizontal
Criteria 3	Fetus in neutral position	Cavum septum pellucidum 1/3 along midline echo	Kidneys not visible	Femoral plane occupying at least 50% of the total image size
Criteria 4	Fetus occupies at least 50% of the total image size	Cerebellum not visible	Multiple ribs not seen	Callipers placed correctly
Criteria 5	Crown and rump clearly seen and callipers are correctly placed	Fetal head occupies at least 50% of the total image size	Abdomen occupies at least 50% of the total image size	
Criteria 6	Yolk sac is not included	Callipers and dotted ellipse placed correctly	Callipers/dotted ellipse are placed correctly	

AC, abdominal circumference; BPD, biparietal diameter; CRL, crown-rump length; FL, femur length; HC, head circumference.

#### Study population

The population eligible for this study are women presenting at a participating facility for an antenatal visit, between 11^+0^ and 13^+6^ weeks gestation. These women can be any age, parity, body mass index and with a singleton or multiple gestation. Pregnant women in whom a major fetal abnormality is known or detected, or where a fetal heart rate cannot be detected, are not eligible.

#### Recruitment

Women attending the participating facilities will be systematically approached by trained research staff and invited to take part in this study, in conjunction with other PEARLS formative research activities. Women with an estimated gestational age of <16 weeks based on best clinical estimate will be invited for screening. During the pre-screening process, an initial, routine conventional scan (gestational age, fetal heart rate) will be performed to assess eligibility. Those eligible for the study (gestational age 11^+0^ to 13^+6^, fetal heart rate present and no known congenital anomaly) will be invited to participate in the study and informed consent obtained prior to data collection. Women who are not eligible or do not consent to participate will receive the same clinical care they would otherwise receive. Study participants will also continue to receive usual clinical care. If an anomaly or absent fetal heart rate is detected during the study (or any other clinical issues are identified) the participant will be referred for appropriate clinical care.

#### Gestational age estimation

##### Conventional ultrasound estimation (standard care)

At each study visit (first and second trimesters), study sonographers will use conventional ultrasound to assess gestational age as outlined in box 1.

Box 1Fetal biometry measurement practice for gestational age estimationWomen in first trimester:Abdominal ultrasound will be used to obtain three crown-rump length (CRL) measurements. The best measurement will be selected, and gestational age will be calculated using INTERGROWTH-21st charts.^23^ The best CRL measurement by clinical judgement and associated image will be entered into Research Electronic Data Capture (REDCap).Women in second trimester:At the second trimester ultrasound, biparietal diameter, head circumference (HC), abdominal circumference and femur length are each measured three times. The best measurement by clinical judgement of each (and associated image) will be entered into REDCap.Gestational age will be estimated using the INTERGROWTH-21 curves based on HC value (mm).^24^

##### Training on the IU FetalCheck device

Prior to the study commencing research midwives attended 1-day training, embedded within a 5-day in person training workshop on the PEARLS cohort and formative studies.^4
5^ Training consisted of an hour lecture on the theory of ultrasound and gestational age estimation, as well as the instructions for using the device, followed by hands-on training, using the device to conduct scans on pregnant women. Training was conducted by a member of the Intelligent Ultrasound team ([name], Intelligent Ultrasound, GE HealthCare).

##### Intelligent ultrasound gestational age estimation

A trained research midwife will complete six abdominal sweeps, as directed by video instruction using the IU FetalCheck device (figure 1). This included three sweeps from the lower abdomen to the upper abdomen, followed by three sweeps left-to-right across the abdomen. The video directs the user on the correct orientation of the probe and maintaining full probe contact with the abdomen as well as guiding them on the sweeps. The required sweeps take an average of 1–2 min to obtain. The IU FetalCheck device has an inbuilt algorithm (V.3.0), which displays the estimated gestational age on the screen.

**Figure 1 F1:**
[figure not shown]
The IU ScanNav FetalCheck. (**A**) The upper portion of the device shows the IU ScanNav FetalCheck software is running on a Microsoft surface. On the lower portion contains the GE VScan Air ultrasound system (two-dimensional grayscale ultrasound with a curvilinear transabdominal probe). (**B**) The visual instructions displayed by the IU ScanNav FetalCheck software, guiding the blind sweeps with the ultrasound probe. GEHC, General Electric HealthCare; IU, intelligent ultrasound.

### Data collection

Research Electronic Data Capture (REDCap), a Good Clinical Practice (GCP)-compliant, web-based data management platform will be used for this study. Screening for the study will be conducted via REDCap, and those eligible will be assigned a participant ID number. All study data included in the case report form as well as de-identified conventional ultrasound images will be directly entered into REDCap using a secure tablet device.

### Participant flow and follow-up

The study comprises two visits for consenting participants (Visits #1 and #2; figure 2). Following eligibility pre-screening (where the gestational age and viability of the pregnancy is confirmed), and informed consent is obtained, Visit #1 is conducted. Participants will have an abdominal ultrasound performed by a study sonographer using the GE VScan Air ultrasound system. The gestational age estimate from conventional ultrasound will be unblinded to the sonographer and participant (as per standard care). The CRL is measured three times and the best measurement by clinical judgement selected. Images from the best measurement will be saved, de-identified and uploaded to REDCap, along with the measurements obtained through the scan. Immediately after, a research midwife will perform a series of abdominal sweeps using the IU system, the estimated gestational age displayed on the IU system screen and the gestational age output from the IU system will be entered into REDCap by the midwife. The sonographer and research midwife will be blinded to each other’s gestational age results to minimise bias. Following the scans, baseline demographic data, blood pressure readings (using the CRADLE VSA device) and anthropometry will be collected from the participant, according to PEARLS procedures.^4^

**Figure 2 F2:**

Flow of participants in the AI ultrasound validation study. AC, abdominal circumference; AI, artificial intelligence; BPD, biparietal diameter; CRL, crown-rump length; FL, femur length; HC, head circumference; IU, intelligent ultrasound; LMP, last menstrual period; USS, ultrasound scan.

Women will be invited to return during the second trimester for Visit #2, at a randomly selected gestational age, between 14^+0^ and 27^+6^ weeks. The timing of Visit #2 is generated randomly in REDCap at the end of Visit #1. During Visit #2, the participant will again receive a conventional ultrasound, performed by a study sonographer. Again, the viability of the fetus will be confirmed via conventional ultrasound and any detected anomalies reported. Fetal biometry measurements will be obtained of the HC, BPD, AC and FL with the images and measurements uploaded directly to REDCap as well as a gestational age estimate according to the second trimester scan (by HC). Immediately after, a research midwife will perform a series of abdominal sweeps using the IU system and the gestational age output will be entered into REDCap. A detailed description of the operational definitions of outcomes is included in online supplemental appendix B, table 1. Where women cannot attend or miss their randomised appointment date (Visit #2, allocated to a 7-day period), women will be invited to attend at the closest available dates, as long as it is before 28 weeks.

### Statistical methods and analysis

#### Quality assessment

Throughout the study, the quality of images collected by sonographers on the conventional ultrasound will be assessed, to ensure high quality images are used for analysis of the gold-standard. For each sonographer, for the first 4 weeks of recruitment, all images will be assessed by the PEARLS ultrasound advisors, as per the criteria described in. For the remainder of the study 20% of the submitted images, selected randomly, will be assessed by the PEARLS ultrasound advisors. If the ultrasound advisors have concerns about the quality of scans from any of the sonographers during the first 4 weeks, that sonographers will continue to have 100% of images assessed throughout the study. Images that fail quality assessment will not be used for final analysis.

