### Data quality assurance

Each study site will be responsible for data entry, as well as investigating and responding to data queries. The data management team will monitor range, consistency and periodic reviews of distributions and identification of outliers. Regular feedback to sites will be used for quality assurance and to improve processes.

To ensure ongoing adherence to the protocol and quality of images, a quality control system will be implemented. The intensity of the quality checks will vary across the life of the project depending on the quality of the scans received. For the first 25 scans from each sonographer, 100% of each conventional scan image will be reviewed by an ultrasound advisor, using the same criteria as the accreditation process. If the study sonographer has provided ≥80% of images with suitable quality, for their next 25 scans only 50% will be reviewed. Subsequent image review will be determined by the quality of data received; this may vary by sonographer. For those sonographers where <80% of images are deemed suitable quality, feedback will be provided and 100% image review will continue for the subsequent 25 scans. For sonographers where <50% of their images are deemed suitable quality, or if they have two scans where the images are unusable for gestational age estimation within a set of 25 scans, the sonographer will be immediately re-trained by both the local team and the ultrasound advisors. Data from each IU device will be periodically synchronised to a secure server, where the participant ID, timestamp, scan video and gestational age estimated by the IU system can be accessed by the data management team. These data are then matched to and cross-checked against the gestational age entered into REDCap to ensure accuracy.

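### The 4-week full-review window closes before almost any second-trimester scan takes place, and the protocol's other image-review scheme covers the gap only in part

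*Protocol article*

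**What the plan says.** The protocol describes image review of the conventional scans in three places.

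- **Quality assessment** (Statistical methods and analysis). For each sonographer, "for the first 4 weeks of recruitment, all images will be assessed by the PEARLS ultrasound advisors". After that, "For the remainder of the study 20% of the submitted images, selected randomly, will be assessed by the PEARLS ultrasound advisors". Full review is extended to the whole study in one stated case: "If the ultrasound advisors have concerns about the quality of scans from any of the sonographers during the first 4 weeks". Images that fail are left out of the analysis.
- **Data quality assurance.** Here the run-in is a count: "For the first 25 scans from each sonographer, 100% of each conventional scan image will be reviewed by an ultrasound advisor". If at least 80% are suitable, "for their next 25 scans only 50% will be reviewed". If fewer are suitable, full review continues for another 25 scans. Below 50%, or with two scans in a set of 25 that cannot be used for dating, the sonographer is re-trained. Beyond that, "Subsequent image review will be determined by the quality of data received; this may vary by sonographer".
- **Training and standardisation.** Before the study, each sonographer submits 10 CRL images and 10 second-trimester scans with BPD, HC, AC and FL. Accreditation needs more than 80% of the submitted images to pass.

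On timing, Participant flow and follow-up states: "The timing of Visit #2 is generated randomly in REDCap at the end of Visit #1", within 14+0 to 27+6 weeks. Box 1 dates the second-trimester pregnancy from HC. HC dating is the comparator for secondary objectives 3 and 4.

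**The concern.** The full-review window in Quality assessment runs on calendar time from the start of recruitment, while second-trimester scans lag enrolment by weeks to months. In its first 4 weeks a sonographer will mostly produce CRL images. The section's one stated route to continued full review depends on concerns raised in that same window, so it responds to CRL quality and hardly at all to HC quality.

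An image that is not reviewed cannot fail and be excluded. If a sonographer takes acceptable CRLs but poor HC planes, a 20% sample leaves most of the poor planes in the analysis. The error in the comparator would then widen the limits of agreement in objective 3 and blur the classification at 20 weeks in objective 4. Both would look like disagreement by the AI system.

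**Working it through.** **Inputs from the protocol.** Visit 1 at 11+0 to 13+6 weeks (days 77 to 97). Visit 2 at 14+0 to 27+6 weeks (days 98 to 195). 13 facilities. 10% loss between visits. The plan's own sample size reproduces: 290/0.9 = 322.2, rounded up to 323 per country, and 3 × 323 = 969.

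**Assumptions, not in the protocol.** Both gestational ages uniform over their ranges, steady accrual, one sonographer per facility, and enrolment lasting 9, 12 or 15 months, or 78 weeks (the text gives April 2025 to Q2-3 2026).

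**1. Gap between visits.** Mean Visit 1 is (77 + 97)/2 = 87 days and mean Visit 2 is (98 + 195)/2 = 146.5 days, so the mean gap is 59.5 days. There are 21 × 98 = 2,058 equally likely day pairs. A gap of d days arises from d pairs for d up to 21, and from 21 pairs for d from 22 to 28. P(gap ≤ 28) = (231 + 7 × 21)/2,058 = 18.4%.

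**2. Share of early enrollees with Visit 2 in the window.** With enrolment uniform over 28 days, the share is the mean of max(0, 28 − gap), divided by 28:

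[Σ(d = 1 to 21) d(28 − d) + 21 × (6 + 5 + 4 + 3 + 2 + 1)] / (2,058 × 28) = (3,157 + 441)/57,624 = 6.2%.

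A simulation of 2 million women gave 6.25%.

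**3. Scans per facility.** 969/13 = 74.5 women. For 12 months, 74.5 × 28/365.25 = 5.7 women enter in the window, and 5.7 × 0.9 × 0.062 = 0.32 Visit 2 scans. The last two columns simulate the Data quality assurance scheme with 75 women per facility (4,000 runs).

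| Enrolment | Women in first 28 days | Visit 2 scans in first 28 days | Visit 2 among first 25 scans | Visit 2 among scans 26–50 |
|---|---|---|---|---|
| 9 months | 7.6 | 0.43 | 4.8 | 10.9 |
| 12 months | 5.7 | 0.32 | 6.1 | 11.6 |
| 15 months | 4.6 | 0.26 | 7.1 | 11.7 |
| 78 weeks | 3.8 | 0.21 | not run | not run |

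**4. After the window, under the 20% rule.** Expected Visit 2 scans per facility: 0.9 × 74.5 = 67. Reviewed: 0.2 × 67 = 13. Not reviewed: 54. As an illustration with an assumed rate, if 40% of one sonographer's HC planes were poor (27 of 67), about 5 would be found and removed and about 21 analysed.

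**5. Does the 80% threshold in Data quality assurance see HC?** Take 19 Visit 1 and 6 Visit 2 scans, one CRL image per Visit 1, and three planes per Visit 2 (Table 1 scores BPD/HC as one). That is 19 + 18 = 37 images. If all six HC planes fail and the rest pass, 31/37 = 84%, and review steps down to 50%. With 5 or 7 Visit 2 scans the figures are 30/35 = 86% and 32/39 = 82%. If BPD and HC count separately and fail together, 31/43 = 72%, and full review continues. The outcome turns on a counting rule that the text does not give.

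**6. Does accreditation see HC?** On the three-plane count there are 10 + 30 = 40 images. Seven of ten HC planes could fail and 33/40 = 82.5% still passes. With BPD and HC counted separately (50 images), four of ten could fail and 42/50 = 84% passes.

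**The case against.** The strongest reply is that Quality assessment does not stand alone. Sonographers are accredited on second-trimester images, HC included, before the study. Data quality assurance then sets a run-in by scan count, not tied to calendar weeks or to the first trimester, with triggers that stay active. On the figures above it would review the 5 to 7 Visit 2 scans in the first 25 and about half of the 11 to 12 in the next 25. Nor does review end at week 4: a random 20% continues, and nothing forbids acting on what it shows.

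Much of this stands. A reader might infer from the 4-week rule that second-trimester biometry is never run in, or that a sonographer with poor HC images cannot trigger full review. The document as a whole does not support either statement, because accreditation and the scan-count triggers both reach such images.

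The reply does not close the point. The two in-study schemes are incompatible (4 weeks then 20%, against 25 scans then 50% then adaptive), and nothing says which governs. If the 4-week scheme governs, the gap remains. If the scan-count scheme governs, the gap narrows, but CRL images can carry a sonographer past the 80% threshold. The re-training trigger for unusable scans helps only in part, since an image can fail the quality score and still yield a date.

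**Conclusion.** The point holds for the Quality assessment section read alone: its full review and its one stated route to continued full review fall in a period with about 0.2 to 0.4 Visit 2 scans per facility, against about 67 expected. Elsewhere the protocol covers part of the gap, but through a conflicting scheme whose threshold pools image types.

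The effect is confined to secondary objectives 3 and 4. A reader might carry it over to the main accuracy result, but primary objectives 1 and 2 compare the AI system with the Visit 1 CRL, which both schemes do cover early on. The size of any bias in objectives 3 and 4 cannot be given, because the protocol states no HC failure rate among accredited sonographers.

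The counts rest on uniform timing, steady accrual and one sonographer per facility. More sonographers per facility would lower each one's count in the 4-week window. A sonographer who starts late, with the window counted from that start, would see more Visit 2 scans in it. This is a cheap improvement, not a threat to the study.

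**What to change.** Merge Quality assessment and Data quality assurance into one scheme based on scan counts, and drop the 4-week window. Apply the existing 25-scan full-review run-in and 80% threshold separately to each sonographer's Visit 1 scans and Visit 2 scans. Keep the escalation trigger active throughout the study, so that poor images found later by sampling restore full review.

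State what is counted: scans or images, and BPD/HC as one or two. This matters within Visit 2 as well: with three planes per scan, 25 scans give 75 images and the threshold is 60, so 15 of 25 HC planes could fail if all others pass. Since HC alone sets the second-trimester date, reporting its pass rate on its own would remove that masking.

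The cost is protocol wording and review time for the existing advisors. Against the 20% rule, the Visit 2 run-in means 25 scans reviewed instead of about 0.2 × 25 = 5, or 20 more per sonographer. Under the 12-month assumption the Visit 1 run-in means 25 instead of about 5.7 + 0.2 × 19.3 = 9.6, or about 15 more. Against the scan-count scheme the increase is smaller. No new staff, scans or visits are needed.
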